### Data analyses

Differences between the intervention and control group in characteristics of participants at baseline will be tested with chi-square tests for categorical variables, Mann-Whitney *U*-test for continuous variables with skewed distributions, and one-way ANOVA for normally distributed continuous variables. Given the hierarchical data structure, multilevel analyses will be used for continuous outcomes, and logistic Generalized Estimated Equation (GEE) analyses for dichotomous outcomes. Logistic GEE is preferred to logistic multilevel analyses because of the instability of the latter. Analyses will be based on an intention-to-treat principle and the level of significance will be set at *p* < 0.05. Missing data will be handled as missing (no imputation). Multilevel analyses will be performed with MLwiN. All other analyses will be performed with IBM SPSS statistics.

With regard to the qualitative data (assessed for the process evaluation), these will be analysed by means of coding techniques based on transcriptions of the qualitative interviews. In the economic evaluation, group averages will be compared using unequal-variance t-tests, according to the intention-to-treat principle. Costs will be compared to QALYs using net-benefit analysis. Multiple imputation will be used to account for missing values. Sensitivity analysis will be performed on the time horizon (base case 6 months vs. 12 months) and the utility measure (base case Dutch EQ-5D tariff vs. visual analogue scale for health).

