### Randomisation (and allocation)

Of the 11 post-acute GR units, six will be randomly allocated by computer-generated randomisation to conduct the FIT-HIP intervention and five are allocated to the control group (usual care). Hip fracture patients will be screened for eligibility for the FIT-HIP study on admission to these post-acute GR units. For this trial, each post-acute GR unit will include a maximum of 15 participants (in order of succession in which patients are admitted to GR, eligible, and willing to participate). Participants will receive treatment (usual care, or the addition of FIT-HIP intervention to usual care) according to the randomisation of the post-acute GR unit to which they are admitted.

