### Sample size

This study tests the null hypothesis that there is no difference in POMA score between the intervention and control group at discharge from GR. The criterion for significance (alpha) was set at 0.050. The test is 2-tailed, which means that an effect in either direction will be interpreted. With a sample size of 40 in both groups, the study will have power of 80% to yield a statistically significant result. Based on our previous research, the minimal clinical relevant difference (mean difference of the POMA at discharge measurement) was set at -3.8, with the common within-group standard deviation at 6.0. The corresponding means are 17.0 vs. 20.8. This effect was selected as the smallest effect that would be important to detect, in the sense that any smaller effect would not be of clinical or substantive significance. It is also assumed that this effect size is reasonable, in the sense that an effect of this magnitude could be anticipated in this field of research.

Compensation for design effect and possible loss to follow-up was taken into account in the choice of sample size. For the design effect (cluster randomisation), the intraclass correlation coefficient (ICC) for the outcome measure POMA is expected to be 0.05 because of clustering of data and because there may be inequality of the numbers within clusters. For the possible loss to follow-up, specifically death in the 3-month rehabilitation phase is not expected be ≥10%. Instead of the 40 patients calculated with the power analysis, we will include 75 patients per group.

As 11 post-acute GR units were interested in participating, we decided to include one additional intervention post-acute GR unit, in case of unsuspected drop-out of one intervention location. Thus, we aim to include a total of 165 participants.

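### Only 11 units are randomised and no small-sample method is named: with the usual large-sample tests the nominal 5% level would be about 7-9% for the primary outcomes at the planning ICC

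*Protocol article*

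**What the plan says.** Under Randomisation (and allocation): "Of the 11 post-acute GR units, six will be randomly allocated by computer-generated randomisation" to the intervention, the other five to usual care, and "each post-acute GR unit will include a maximum of 15 participants".

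Under Data analyses, continuous outcomes get multilevel models and dichotomous outcomes get logistic GEE. Significance is set at p below 0.05. On software, "Multilevel analyses will be performed with MLwiN", with SPSS for the rest. The reason given for GEE is "Logistic GEE is preferred to logistic multilevel analyses because of the instability of the latter". The section does not state ML or REML, a z or t reference, or which GEE variance estimator is used.

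Under Sample size, "The criterion for significance (alpha) was set at 0.050" and two-sided. Clustering enters through a design effect, where "the intraclass correlation coefficient (ICC) for the outcome measure POMA is expected to be 0.05". The two primary outcomes, POMA and FES-I at discharge, are continuous.

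**The concern.** The arm is assigned to units, so its effect is estimated from 11 unit-level results, with 11 - 2 = 9 degrees of freedom. Large-sample tests treat the standard error as known. An uncorrected GEE sandwich is also biased downward when there are only five or six clusters per arm. Used in their ordinary large-sample form, both named methods would reject more often than the stated 5% and give intervals that are too short. The planned power has the same gap: a design effect inflates the variance but does not account for the few degrees of freedom.

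**Working it through.** **Inputs from the article.** 6 + 5 units; at most 15 per unit; ICC 0.05; two-sided alpha 0.05; difference 3.8; SD 6.0; deaths below 10%. The Sample size section foresees the possible loss of one intervention unit, which gives 5 + 5.

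**The plan's own figures reproduce.** A difference of 3.8 with SD 6.0 needs 40 per group (t-test power 79.9%). The design effect is 1 + 14 x 0.05 = 1.70, and 40 x 1.70 = 68. Then 68 / 0.9 = 75.6, or 68 x 1.1 = 74.8, in line with the stated 75.

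**Analytic check.** A cut-off of 1.96 applied to a t statistic on 9 df rejects in 8.2% of null trials.

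**Why the sandwich is too small.** Take equal unit sizes and let SS be the within-arm sum of squares of unit means. The uncorrected variance is SS1/36 + SS0/25. The unbiased one is SS1/(6 x 5) + SS0/(5 x 4). The expected ratio is (5/36 + 4/25) / (1/6 + 1/5) = 0.299 / 0.367 = 0.82, so the standard error is about 10% too small (square root 0.90) even before the choice of z or t.

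**Null simulation.** 40,000 trials per setting, 13 or 15 analysed per unit, z tests, no correction. ICC is 0.05 in the first three rows. The logistic row covers event rates 0.1-0.5 and ICC 0-0.1.

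| Method | 6 + 5 units | 5 + 5 units |
|---|---|---|
| Multilevel, REML | 6.7-6.8% | 6.9-7.3% |
| Multilevel, ML | 8.7-8.9% | 8.8-9.4% |
| GEE, continuous data | about 11.2% | 11.8-12.0% |
| Logistic GEE, binary data | 9.3-11.6% | 10.0-11.9% |

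The Monte Carlo standard error is about 0.1-0.2 percentage points; for example, the square root of 0.07 x 0.93 / 40,000 is 0.13 points. With unit sizes varying from 5 to 15 (4,000 trials), REML gave 6.9% and ML 8.3%. A separate simulation with 13 per unit gave 6.7% and 8.5%. Multilevel inflation depends on the ICC: 4-6% at ICC 0-0.01 and 8-12% at 0.1-0.2. GEE inflation hardly does.

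**With corrections (null rejection).**
- t-test on unit means: 4.9-5.2% at ICC 0.05.
- REML with t on K - 2 df (K = number of units): 3.7-4.0% at ICC 0.05, about 5% at ICC 0.2.
- GEE, Kauermann-Carroll variance and t: 4.9-5.0%; 4.3-4.9% in the separate simulation.
- GEE, Mancl-DeRouen variance and t: 3.3-3.4%.
- GEE, uncorrected variance and t: about 7.2%, so the t reference alone does not repair it.

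**Power at the planning inputs.** With m analysed per unit, SE = 6.0 x sqrt{[1 + (m - 1) x 0.05] / m x (1/k1 + 1/k0)}. For 6 + 5 and m = 15 this is 6.0 x sqrt(1.70/15 x 0.367) = 1.22, and 3.8 / 1.22 = 3.11. The value m = 13.5 is 15 less 10%.

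| Units, m | Power, z | Power, t on K - 2 df |
|---|---|---|
| 6 + 5, 15 | 87.4% | 78.9% |
| 6 + 5, 13.5 | 85.4% | 76.5% |
| 5 + 5, 15 | 84.5% | 74.1% |
| 5 + 5, 13.5 | 82.3% | 71.6% |

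**The case against.** The strongest reply is that the article names model families and a significance level but not the estimator, the reference distribution or the GEE variance. Those details are often left to an analysis plan, which may exist and may contain a correction. That stands in part: the error rates are conditional, and the article neither states nor excludes uncorrected tests. It does not dispose of the point. The article fixes the number of units, the methods and the 5% level, and standard use of those methods misses that level. Its sample size also allows for clustering only through a variance inflation.

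Four stronger readings are tempting, and the documents do not support them.
- A reader might infer that the stability argument for GEE is mistaken. The article compares GEE with logistic multilevel models and claims nothing about small-sample error rates. No logistic multilevel model was simulated here, so the argument is untested, and GEE remains usable once corrected.
- A reader might apply the 10-12% figure to the main conclusion. It concerns dichotomous outcomes only, such as mortality, and none of these is primary.
- A reader might take the multilevel inflation as certain. It disappears as the ICC approaches zero.
- A reader might conclude that the named packages cannot do the corrections. Nothing in the article says so.

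**Conclusion.** The point holds in conditional form. If large-sample tests are used without correction, each primary outcome carries a false-positive risk of about 7% (REML) to 9% (ML) at the plan's own ICC, and dichotomous secondary outcomes carry about 10-12%. This assumes z tests, an uncorrected sandwich for GEE, and 13 to 15 analysed per unit. For the primary outcomes the inflation is moderate, and the true ICC decides whether it is negligible or larger. The power consequence does not depend on which test is finally chosen: any test that respects 8 or 9 degrees of freedom at the planning inputs falls somewhat short of 80%.

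**What to change.** Prespecify the following before the data are analysed.
- **Continuous outcomes:** a multilevel model fitted by REML with a Kenward-Roger or Satterthwaite reference distribution, or a t-test on (adjusted) unit means with 9 df (8 if one unit is lost). The Kenward-Roger and Satterthwaite options were not simulated here. The plain K - 2 version of REML was somewhat conservative.
- **Dichotomous outcomes:** keep GEE, with a bias-corrected sandwich such as Kauermann-Carroll and a t reference on the same df, or use a unit-level analysis. Mancl-DeRouen with t is also valid but somewhat conservative.
- **Sample size:** recompute and restate power with a t reference.

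The change is to analysis wording and touches no patient procedure. Its price is larger p-values and wider intervals: for a given standard error, moving from 1.96 to the 9-df value of 2.262 widens an interval by 2.262 / 1.96 = 1.15, or 15%. Power at the planning inputs becomes about 72-79% instead of 82-87%.

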### Effect evaluation

#### Primary outcome

1. Mean difference in the Tinetti Performance Oriented Mobility Assessment (POMA) score [32, 33] at discharge from GR (or at a maximum of 3 months after admittance to GR), compared between FIT-HIP intervention and usual care. The POMA is a measure of mobility function (gait and balance).

2. Mean difference in the Falls Efficacy Scale International (FES-I) score [34–36] at discharge from GR (or at a maximum of 3 months after admittance to GR), compared between FIT-HIP intervention and usual care. The FES-I is a measure of fear of falling.

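### As described, the effect analysis rests on observed discharge scores alone and names no pre-intervention covariate; specify a baseline term, the missing-data assumption and a sensitivity analysis

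*Protocol article*

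**What the plan says.** The Primary outcome section defines POMA and FES-I each as a mean difference in score "at discharge from GR (or at a maximum of 3 months after admittance to GR), compared between FIT-HIP intervention and usual care". The Sample size section tests the POMA difference at that same point.

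The Data analyses section gives multilevel models for continuous outcomes and logistic GEE for dichotomous ones, under an intention-to-treat principle, and adds: "Missing data will be handled as missing (no imputation". For the economic evaluation the same section says: "Multiple imputation will be used to account for missing values".

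On loss, the Sample size section says: "Compensation for design effect and possible loss to follow-up was taken into account in the choice of sample size". It names death during the 3-month rehabilitation phase, expected to stay below 10%.

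The section on the duration of the intervention lists length of stay, number and duration of therapy sessions, and performance of the intervention components as variables that may serve as confounders in the final outcome analyses. No other covariate is named for those analyses.

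Table 1 places the Barthel index, Functional Ambulation Categories (FAC) and 10 m walk test at baseline and discharge, and EQ-5D at baseline, discharge and both follow-ups. It does not list POMA or FES-I, whose only stated time point in the readable text is discharge. Fig. 1, which outlines the procedures, is not visible in the text reviewed.

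**The concern.** Three features combine.

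- **Single time point, no imputation.** A model of the discharge score alone drops every patient who lacks it. Enlarging the sample for expected loss protects power; it does not protect against bias if those lost differ between arms. The loss that the plan names is death, which in this population is plausibly related to the function that POMA measures.
- **Covariates.** The only adjusters named are consequences of treatment or part of it. Performance of intervention components is recorded in the intervention arm only. Adjusting for such variables can remove part of the effect being estimated. A pre-intervention functional measure has no such drawback, yet none is named. It would also help against imbalance: there are only 11 units, and patients are recruited at units whose staff know the allocation.
- **EQ-5D.** The same instrument is left unimputed as a secondary effect outcome and falls under multiple imputation as the source of QALYs, with no reason given. The two sets of results may then rest on different patients.

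At stake are precision on POMA and FES-I and some protection of the primary contrast against loss and recruitment imbalance.

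**Working it through.** **Inputs from the Sample size section.** Two-sided alpha 0.05; 40 per arm for 80% power; a POMA difference that "was set at -3.8, with the common within-group standard deviation at 6.0"; ICC 0.05; loss below 10%. The Randomisation section gives 15 patients per unit and 6 versus 5 units.

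**Plan's own figures.**
- n per arm = 2 × (1.96 + 0.8416)² × 6.0² / 3.8² = 39.1, so 40. Power at 40 is 80.9% by the normal approximation and 79.9% by the exact t.
- Design effect = 1 + (15 − 1) × 0.05 = 1.7; 40 × 1.7 = 68.
- 68 / 0.90 = 75.6, or 68 × 1.10 = 74.8. The stated 75 reproduces. No baseline correlation enters.

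**Precision without a baseline term, 10% lost.**
- Completers per unit: 15 × 0.9 = 13.5. Design effect = 1 + 12.5 × 0.05 = 1.625.
- Effective n: 6 × 13.5 / 1.625 = 49.8 and 5 × 13.5 / 1.625 = 41.5.
- SE = 6.0 × √(1/49.8 + 1/41.5) = 1.26 points.
- Power for 3.8 points: 85.4% by the normal approximation, 76.5% by noncentral t on 6 + 5 − 2 = 9 df.

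**With a baseline term.** The residual SD becomes 6.0 × √(1 − r²), with the ICC held at 0.05. The documents give no r, so a range is assumed.

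| r (assumed) | SE | SE reduction | Power, normal | Power, 9 df |
|---|---|---|---|---|
| none | 1.26 | – | 85.4% | 76.5% |
| 0.3 | 1.20 | 5% | 88.5% | 80.3% |
| 0.5 | 1.09 | 13% | 93.6% | 87.1% |
| 0.7 | 0.90 | 29% | 98.8% | 96.2% |

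**Bias of the available-case difference.** If fractions f₁ and f₂ are missing and the missing patients would have scored D points differently from those expected, bias ≈ (f₁ − f₂) × D. All values here are assumptions.
- Equal loss and equal gaps: 0.
- 10% versus 5%, D = 2 to 6 points: 0.05 × 2 = 0.1 to 0.05 × 6 = 0.3 points.

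**Equal loss, different mechanism.** In a simulation without clustering, about 10% were lost in each arm. Loss was random in the intervention arm and concentrated among low baseline scores in the control arm. With a true difference of 3.8, the unadjusted available-case difference was 3.59, 3.50 and 3.39 at r = 0.3, 0.5 and 0.7. Adding the baseline score gave 3.79, 3.80 and 3.81, with no imputation.

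**The case against.** The strongest reply is that this is a condensed article. It names a model class and leaves model structure and covariates to fuller documents. Nothing excludes a baseline covariate or a repeated-measures multilevel model, and the latter needs no imputation under missing at random. That stands: a reader might infer that the plan forbids baseline adjustment, but the article is merely silent. Nor can the readable text confirm that POMA or FES-I is measured at baseline.

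A reader might also infer that not imputing breaks intention to treat. It does not do so by itself, as the simulation shows: a likelihood model containing the baseline score recovered the true difference from the observed patients.

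A reader might infer an underpowered trial from the 76.5%. The plan's figures reproduce, allow for 10% loss and give 82% power with 5 versus 5 units or 85% with 6 versus 5 on its own normal approximation. The lower figure comes from the 9-df reference distribution, which is a separate matter.

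The two EQ-5D treatments are not contradictory either. QALYs accumulate over 6 months and need a complete series, whereas the effect comparison is at discharge. The split is unexplained, no more.

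Two further limits hold. Logistic GEE needs stronger missingness assumptions if neither weighted nor imputed, but it does not touch the continuous primary outcomes. And imputing a POMA score for patients who died is no obvious remedy.

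What the reply does not answer is that the no-imputation rule is stated, the outcomes are defined at discharge only, and the one set of adjusters that the article does name is post-randomisation.

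**Conclusion.** The point holds as an improvement that should be made. As described, the effect analysis uses observed discharge scores only, and the only adjusters named arise after randomisation. A pre-intervention measure would reduce the SE by about 5%, 13% or 29% and raise 9-df power from 76.5% to about 80%, 87% or 96% (normal approximation: 85% to about 88%, 94% or 99%). These gains rest on assumed correlations of 0.3, 0.5 and 0.7 and an unchanged ICC. They improve on a calculation that already meets its own target.

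Bias from differential loss cannot be sized from the documents: it is zero with equal loss and equal gaps, and 0.1 to 0.3 points for 10% versus 5% loss with a 2 to 6 point gap. A reader might build a larger figure, such as 15% versus 5% loss with a 6-point gap, giving 0.10 × 6 = 0.6 points or 16% of 3.8. The documents support neither that imbalance nor that gap; they expect deaths below 10% and give no difference between arms.

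**What to change.** 1. Specify the primary multilevel model: random unit effect, arm, and the baseline value of the same scale if it is measured. If it is not, use one pre-specified baseline functional measure already collected (Barthel, FAC or 10 m walk). For scales measured at baseline, a longitudinal multilevel model of all time points is an alternative, valid under missing at random without imputation.
2. Keep length of stay, therapy quantity and component performance out of the primary effect model.
3. State the missing-data assumption and add a sensitivity analysis, for example multiple imputation that respects clustering. The imputation planned for the economic data is not described as doing so, and it cannot simply be assumed to carry over.
4. Report deaths separately by arm, with a sensitivity analysis for their handling.
5. Align the EQ-5D handling between the effect and economic analyses, or give the reason for the difference.

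**Cost:** wording and modest extra programming, with no new data collection. The price is a missing-at-random assumption that has to be stated openly.

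### The economic evaluation compares arms with patient-level t-tests although 11 units are randomised, so its standard errors are too small for any positive intraclass correlation

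*Protocol article*

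**What the plan says.** The unit of randomisation is the rehabilitation unit. The section Randomisation (and allocation) states: "Of the 11 post-acute GR units, six will be randomly allocated by computer-generated randomisation to conduct the FIT-HIP intervention and five are allocated" to control, and "each post-acute GR unit will include a maximum of 15 participants".

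The Sample size section budgets for this: "the intraclass correlation coefficient (ICC) for the outcome measure POMA is expected to be 0.05". The Data analyses section follows through for the effect evaluation: "Given the hierarchical data structure, multilevel analyses will be used for continuous outcomes", with logistic GEE for dichotomous outcomes.

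The next paragraph of that section sets a separate rule for the economic evaluation: "In the economic evaluation, group averages will be compared using unequal-variance t-tests", by intention to treat. It continues: "Costs will be compared to QALYs using net-benefit analysis". Missing values there are multiply imputed. The two sensitivity analyses listed concern the time horizon and the utility measure. Nothing in the economic rule refers to units or clustering.

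**The concern.** The unequal-variance (Welch) t-test relaxes the assumption of equal variances. It does not relax the assumption that observations are independent. Patients in one unit share therapists, a care pathway and an organisation, so their costs and QALYs may be correlated. When whole units are randomised, that correlation adds directly to the variance of the difference between arms, and a patient-level test leaves it out.

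The same section accepts this argument for the clinical outcomes, so the economic rule is inconsistent with the plan's own reasoning. At stake is the stated certainty of the cost and QALY comparisons. The same understatement carries into the net-benefit analysis if that rests on these tests. Cost-effectiveness is part of the trial's stated aim in the Abstract and Background.

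**Working it through.** **Inputs.** Units: 6 v 5; patients per unit: m = 15 at most (Randomisation). ICC for POMA: 0.05; POMA difference 3.8, SD 6.0; power 80%; loss below 10% (Sample size). Test level: "The criterion for significance (alpha) was set at 0.050", two-sided. ICC for costs and QALYs: not given, so assumed over a range.

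**The plan's own figure first.**
- Unadjusted n per group = 2 × (1.96 + 0.84)² × 6.0² / 3.8² ≈ 39.1, rounded up to 40, as stated.
- Design effect: DE = 1 + (m − 1) × ICC = 1 + 14 × 0.05 = 1.70.
- 40 × 1.70 = 68. Allowing for 10% loss, 68 × 1.1 = 74.8 or 68 / 0.9 = 75.6. The plan's 75 per group is reproduced.

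So a design effect of 1.70 accounts for the plan's sample size for POMA.

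**Effect on the economic t-tests.** The true standard error is √DE times the one that the t-test uses. The t-test's standard error is therefore too small by 1 − 1/√DE, and the approximate type I error is 2 × [1 − Φ(1.96/√DE)].

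With m = 15:

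| Assumed ICC | DE | t-test SE ÷ true SE | Type I error, formula | Type I error, simulation |
|---|---|---|---|---|
| 0 | 1.00 | 1.00 | 5.0% | 5.0% |
| 0.01 | 1.14 | 0.94 | 6.6% | 6.4% |
| 0.02 | 1.28 | 0.88 | 8.3% | 8.3% |
| 0.05 | 1.70 | 0.77 | 13.3% | 13.2% |
| 0.10 | 2.40 | 0.65 | 20.6% | 20.6% |

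The simulation used normal data, 6 v 5 units of 15 and 40,000 replicates per row.

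With 10% loss, m = 13.5 and ICC 0.05: DE = 1 + 12.5 × 0.05 = 1.625, SE ratio 0.784, type I error 12.4%. At ICC 0.05 the standard error is thus 22–23% too small. With m = 15, a nominal 95% interval covers about 100 − 13.3 ≈ 87%.

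**Does a unit-level analysis repair it?** In the same simulations, an ordinary t-test on the 11 unit means (11 − 2 = 9 df) rejected in 4.8% to 5.1% of replicates at every ICC in the table, and in 4.9% at ICC 0.05.

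**Cost in interval width at ICC 0.05.** The larger standard error alone widens the interval by √1.625 = 1.27 to √1.70 = 1.30. Using 9 df as well (t = 2.26 against about 1.98) multiplies this by about 1.14, so a valid interval is about 46–49% wider than the planned one.

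**The case against.** **The general sentence might cover costs and QALYs.** They are continuous outcomes. But the economic paragraph names its own test, just as its multiple imputation replaces the no-imputation rule given for the other analyses. The specific rule governs.

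**The ICC of 0.05 is given for POMA only.** This stands. A reader might infer that the economic tests have a 13% false-positive rate. The documents support that only conditionally on the borrowed ICC.

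**Costs may cluster less than POMA.** A reader might infer that costs depend on the unit at least as much as POMA does. The article does not show this and partly points the other way:
- Duration of the FIT-HIP intervention says that length of stay is decided patient by patient.
- The Economic evaluation section sets a 6-month horizon after discharge. Apart from the intervention itself, it lists mainly care delivered outside the unit, valued at standard prices.
- The Discussion expects only slight differences in usual care between units.

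On the other side, Usual care (control group) places therapy intensity in each unit's own care pathway. Some clustering is therefore plausible, but its size is open.

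**No uncertainty method is stated for net benefit.** This also stands. The article names no interval and no variance method for that step, so the point reaches it only if it is built on the t-tests.

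**The matter is secondary.** The economic evaluation is the last of the secondary objectives, and the primary outcomes are continuous and fall under the multilevel rule. This limits the severity but does not make the test suitable for the design.

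**Conclusion.** The point holds as a stated method that does not fit the design. Patient-level unequal-variance t-tests in a trial of 11 randomised units give standard errors that are too small, and a type I error above 5%, for any positive ICC in costs or QALYs. Neither listed sensitivity analysis would reveal this.

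The size depends on an ICC that the documents do not give. With 15 patients per unit, type I error is about 7%, 8%, 13% and 21% at assumed ICCs of 0.01, 0.02, 0.05 and 0.10. The percentages assume equal unit sizes and normal data; the direction needs only a positive ICC.

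A reader might infer that the cost-effectiveness result itself would be biased or tilted in favour of the intervention. That does not follow: ignoring clustering understates uncertainty and does not by itself shift the estimated differences. Severity: should-fix, for a secondary objective.

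**What to change.** Replace the t-test sentence with a comparison that accounts for rehabilitation unit. Either of these would do:
- a mixed model for cost, QALY and net benefit with a random effect for unit and small-sample degrees of freedom; or
- a t-test on the 11 unit means (9 df), which is simpler and held its level in the check above.

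Include unit in the multiple-imputation model, so that imputed values keep the between-unit variation. State that the uncertainty of net benefit comes from the same analysis.

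Adjusting QALYs for baseline EQ-5D, which is already collected (Table 1), is an optional further gain and not part of the error.

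The change is to analysis wording only. It needs no new data and leaves recruitment and the primary analyses as they are. The downside is wider intervals for the economic results.
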